#### Dosing schedule and administration

Patients in the TAU group (n=84) will receive the standard dosing regimen of 300 mg of secukinumab as weekly injections for 5 weeks (weeks 0–4), followed by 3 monthly injections in weeks 8, 12 and 16. The injections will be administered by the research assistant to ensure that the study physician remains blinded to group allocation. Patients in both reinforcement groups will initially receive weekly injections of 300 mg of secukinumab during an acquisition phase (weeks 0–1). After the acquisition phase, patients in the partial reinforcement group will receive alternating weekly injections of 150 mg of secukinumab or a placebo (ie, sodium chloride) for 3 weeks (weeks 2–4) followed by monthly injections in weeks 8, 12 and 16. Injections for the patients in the continuous reinforcement group will be administered in the same weekly and monthly schedule as in the other experimental group but will consist of a continuous dose of 75 mg of secukinumab. Both reinforcement groups will receive the same total amount of medication to ensure that any observed effects will be attributable to the pharmacological conditioning, rather than differences in the total doses of the medication in the TAU and partial reinforcement group.

Additionally, at each visit, patients in both reinforcement groups will be given a novel-tasting gustatory stimulus (ie, 100 mL of fruit milk dyed with green food colouring and infused with lavender oil) right before medication or placebo administration. The research assistant will conduct the administration of the beverage, accompanied by standardised information about its potential benefits via a medical educational video, which was developed in collaboration with the Collaborative Research Center’s (CRC) patient advisory board.

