### Outcomes

#### Primary outcomes

##### Itch

The change in itch severity will be assessed as primary outcome throughout the intervention and follow-up phase. Participants will be asked to rate the most severe itch as well as the average itch experienced over the last 24 hours on a Visual Analogue Scale (VAS). The scale ranges from 0 (‘no itch’) to 100 (‘most severe itch imaginable’). Specifically, participants will be asked: ‘How severe was the most intense itch you experienced in the last 24 hours?’ (German: ‘Wie stark war der schlimmste Juckreiz, den Sie in den letzten 24h gespürt haben?’) and ‘How severe was your average itch in the last 24 hours?’ (German: ‘Wie stark war Ihr durchschnittlicher Juckreiz in den letzten 24h?’). This measurement will be carried out during visits 1–9.

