### Sample size, group allocation and blinding

#### Sample size

To test the non-inferiority of the drug-dose reduction strategy to the standard care at an exploratory level, the sample size calculation was conducted in R using the epiR package (function: epi.ssninfb). This calculation is based on a non-inferiority framework using the absolute risk difference scale. For the purpose of calculation, a favourable outcome was assumed for 70% of participants in the reinforcement group and 75% in the TAU group. The non-inferiority margin was set to an absolute risk difference of 0.25, corresponding to a minimal clinically important difference (MCID) of >25%. Assuming a one-sided α=0.05 and 80% power, a total sample size of N=152 was required for a 1:1 comparison between TAU and the pooled reinforcement groups. As the primary non-inferiority hypothesis compares TAU with the pooled reinforcement groups, the sample size calculation was based on a 1:1 allocation ratio.

To account for the dropout rate of 10% during a previous study, which investigated the impact of verbal inductions of positive treatment-related expectations as a dose-reduction strategy in patients with psoriasis,^33^ a sample size of N=168 is set.

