We hypothesise that symptom trajectories differ between groups. Specifically, both experimental groups are expected to show slower improvements in objective disease severity (ie, PASI scores), while improvements in subjective symptoms (ie, itch and DLQI scores) are expected to be comparable to those in the TAU group. Group × Time interactions will be modelled to identify differential symptom trajectories. Given the absence of prior data on the exact shape of these trajectories, no assumptions about their functional form are made beyond the directionality stated above. Post hoc contrasts will be conducted to explore group differences at specific time points or in change patterns across the study period.

#### Hypothesis 3

As part of hypothesis 3, we examined potential effects on secondary outcomes, namely side effects. Specifically, we hypothesise that participants in the experimental groups (pooled across partial and continuous reinforcement) will report fewer side effects from pre to post compared with the TAU group. A linear mixed model with a Group × Time interaction will be fitted to side effect scores derived from the GASE questionnaire.

#### Hypothesis 4

Supplementary to the other hypotheses, a subsequent analysis focusing on the two reinforcement groups will examine potential differences in both overall and longitudinal effects of the various dosing regimens. We hypothesise that the partial reinforcement group will show stronger treatment effects on outcomes compared with the continuous reinforcement group. Specifically, we expect significantly greater average reductions in itch, PASI and DLQI scores over time. This hypothesis will be tested via the Group × Time interaction across all 10 measurement points. If the interaction is significant, follow-up contrasts will compare the estimated change trajectories between the two experimental groups, with a focus on overall pre–post improvement and the rate of change over time.

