### Missing data handling

All primary analyses will follow the intention-to-treat (ITT) principle, including all patients who received at least one active dose of the study medication and completed the acquisition phase (ie, attended visits 0–2). Patients meeting this criterion will be included in the analysis with all available data up to the point of dropout. By contrast, individuals who only attended the baseline assessment (visit 0) will be excluded from longitudinal modelling due to the absence of any post-baseline intervention exposure (ie, no medication or conditioned stimulus was administered). Missing data will be addressed using Full Information Maximum Likelihood (FIML) as the primary estimation approach. FIML leverages all available data points, including partially observed cases, by estimating model parameters based on the observed-data likelihood, without imputing missing values. This method is particularly suitable for complex mixed-effects models and preserves statistical power while minimising bias under the assumption of data missing at random (MAR).

Given the structured nature of data collection, where all assessments are completed on-site prior to medication administration, only a low proportion of missing data is expected. Reasons for missed visits (eg, illness, psychological burden) will be documented systematically through physician–patient contact and follow-up communication. In addition, a wide range of psychometric, demographic and clinical variables (eg, depression, anxiety, acute stress, treatment satisfaction) is collected, which increases the possibility that missingness is conditionally random (ie, MAR) and can be accounted for by observed data.

To empirically evaluate the MAR assumption, we will conduct logistic regression analyses to identify variables that significantly predict the occurrence of missing data. If no such variables are found, the originally specified analysis model will be estimated using FIML, without the inclusion of auxiliary covariates, thereby ensuring consistency with the pre-specified hypothesis structure.

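### Hypothesis 4 is directional, but the contrast that answers it is run only after a non-directional Group × Time test, which can block a real effect

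*Protocol article*

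**What the plan says.** Protocol article, Analysis plan, Hypothesis 4: for partial against continuous reinforcement, "we expect significantly greater average reductions in itch, PASI and DLQI scores over time". The test follows: "This hypothesis will be tested via the Group × Time interaction across all 10 measurement points". The contrasts are conditional: "If the interaction is significant, follow-up contrasts will compare the estimated change trajectories between the two experimental groups", with attention to pre–post improvement and rate of change.

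The opening of the Analysis plan makes Time a 10-level factor, one level per visit, and sets α at 0.05 for confirmatory tests. No one-sided test is stated for Hypothesis 4. For itch, the Itch section says: "This measurement will be carried out during visits 1–9".

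Two other places matter for the fix. Under Dosing schedule and administration, both reinforcement arms receive 300 mg in weeks 0 and 1 and differ only from week 2. Under Missing data handling, the visits are described as ones "where all assessments are completed on-site prior to medication administration".

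**The concern.** The claim is a single signed quantity: the difference between two arms in how far the scores fall. The test asks whether the two visit profiles differ in any way at all. It can be significant because continuous reinforcement does better, or because the curves cross without any difference in overall improvement. Conversely, a real advantage for partial reinforcement must first be large enough to show against 9 degrees of freedom before the contrast that measures it is looked at.

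This comparison matters more than its place as the last hypothesis suggests. It is the only one in the trial between groups with equal total dose, and the Trial design section relies on it to separate dose from conditioning. It has about 42 patients per arm, so there is little power to spare.

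**Working it through.** **No plan figure to reproduce.** The Sample size section sizes only the pooled comparison with TAU. It gives no effect size, SD or power for Hypothesis 4.

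**Inputs from the document.** N = 168 at 2:1:1 gives 84/42/42. Two arms over 10 visits give (2−1)(10−1) = 9 df; itch, with 9 visits, gives 8. Eight injections at visits 1–8 fall in weeks 0, 1, 2, 3, 4, 8, 12 and 16. Assessment precedes injection and the doses first differ in week 2, so visits 0–3 are all measured before the arms diverge.

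**Assumptions.** Difference of 0.4 SD at the end; total variance 1; equal correlation r = 0.5 between visits (the structure that a random intercept implies); no dropout; arms identical through visit 3. Four sustained shapes after that: (a) linear by visit, (b) linear in weeks, (c) constant from visit 4, (d) present at visits 8–9 only.

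**Cost of the degrees of freedom.** At α = 0.05, 80% power needs a noncentrality of 15.65 on 9 df and 7.85 on 1 df. The contrast wins if it captures more than 7.85/15.65 = 50% of the pattern.

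**Formulas, worked for shape (c).**
- Interaction: λ = (n/2) × Σ(δ − mean δ)² / (1−r). Six of ten visits carry 0.4, so the sum is 0.16 × 10 × 0.6 × 0.4 = 0.384, and λ = 21 × 0.384/0.5 = 16.13.
- Contrast, visits 0–3 to mean of 8–9: λ = 0.16 / [(1/4 + 1/2) × (2/42) × 0.5] = 8.96, a share of 8.96/16.13 = 0.56.
- Contrast, visit 0 to mean of 8–9: λ = 0.16 / [(1 + 1/2) × (2/42) × 0.5] = 4.48. Using one reference visit instead of four doubles the variance.

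The shares for the visits 0–3 contrast are 0.86 / 0.85 / 0.56 / 0.83 over shapes (a) to (d).

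**Power by simulation** (contrast at two-sided 5%, counted only in the predicted direction):

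| | (a) | (b) | (c) | (d) |
|---|---|---|---|---|
| Interaction alone | 0.49 | 0.46 | 0.81 | 0.60 |
| Visits 0–3 reference, ungated | 0.79 | 0.76 | 0.85 | 0.85 |
| Same contrast, gated | 0.47 | 0.43 | 0.74 | 0.58 |
| Visit 0 reference, ungated | 0.50 | 0.47 | 0.56 | 0.57 |
| Same contrast, gated | 0.34 | 0.31 | 0.51 | 0.43 |

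For itch (reference visits 1–3, 8 df): 0.71–0.81 ungated, 0.42–0.66 gated. With 38 per arm (N = 152), visits 0–3 reference: 0.74 / 0.72 / 0.81 / 0.81 ungated, 0.42 / 0.39 / 0.68 / 0.52 gated.

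**Sensitivity.** Over 0.3–0.5 SD and r from 0.3 to 0.7, the gate costs 0 to 0.33 (visits 0–3 reference) or 0 to 0.16 (visit 0 reference).

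**A case against the contrast.** For a 0.4 SD difference at visits 4–6 only, the interaction has λ = 21 × (0.16 × 10 × 0.3 × 0.7)/0.5 = 14.11 and power 0.74. The contrast has none beyond its one-sided error, about 0.03.

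**The case against.** The best defence is that Hypothesis 4 has two aims. Its text speaks of overall and longitudinal effects and of reductions over time, and its follow-up covers both improvement and rate of change. An interaction followed by contrasts is a conventional way to serve both. Change from baseline lies inside the Group × Time space, and the contrasts would show direction. Under Hypothesis 2 the plan also explains that the shape of the trajectories is unknown.

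Much of this stands. The interaction is a legitimate analysis, and it is not always the weaker one. With visit 0 as reference, the ungated contrast (0.50 / 0.47 / 0.56 / 0.57) has no real advantage over the interaction itself (0.49 / 0.46 / 0.81 / 0.60). The larger gain comes from the pre-divergence reference and a sustained effect, and the protocol specifies neither. The covariance matters too. With serial correlation (0.7 per four weeks) and an effect constant from visit 4, scaled so that a contrast of visits 4–9 with visits 0–3 has power 0.80, the interaction reaches 0.95.

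What does not stand is the conditional rule. Whichever contrast is chosen, requiring a significant interaction as well can only remove rejections. Hypothesis 2 makes few assumptions about form, so an omnibus test suits it; Hypothesis 4 names its quantity and its sign. Being called supplementary does not make it exploratory, since the exploratory analyses are set apart in the next section.

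Three stronger readings are tempting and are not supported:
- A reader might infer that alternating 150 mg with placebo biases the test through drug levels at single visits. The document gives no half-life or dose-response, and under assumed values a false claim in favour of partial reinforcement had probability at most 0.016. This is no ground for the point.
- A reader might take the reference to 10 measurement points as a serious error for itch. The model would simply fit nine levels.
- A reader might infer that the dosing section misidentifies the groups with equal dose. It names them correctly ("Both reinforcement groups will receive the same total amount of medication to ensure that any observed effects will be attributable to the pharmacological conditioning") and slips only in its last clause ("rather than differences in the total doses of the medication in the TAU and partial reinforcement group"). Totals are TAU 8 × 300 = 2400 mg, partial 2 × 300 + 3 × 150 = 1050 mg and continuous 2 × 300 + 6 × 75 = 1050 mg. No analysis depends on the slip.

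**Conclusion.** The point holds as a mismatch between a directional hypothesis and its stated decision rule. It is worth correcting but does not invalidate the analysis. The mismatch and the fact that the gate cannot help follow from the text alone. The size of the loss does not: it rests on an assumed effect, correlation, covariance structure and set of shapes. Under those assumptions (0.4 SD, r = 0.5), gating lowers the power of a given contrast by 0.11 to 0.33 with visits 0–3 as reference and by 0.05 to 0.16 with visit 0. The harm is lost power and an unclear reading of a significant interaction, not false claims for partial reinforcement.

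**What to change.** Make one pre-specified 1-df contrast the test of Hypothesis 4 for each outcome, not conditional on the interaction: partial minus continuous, change from the mean of visits 0–3 (visits 1–3 for itch) to the mean of visits 8 and 9, at two-sided 5%, with support claimed only in the predicted direction. Keep the Group × Time interaction and the trajectories as supportive analyses. If visit 0 is preferred as the reference, still remove the gate, but expect no power advantage over the interaction itself.

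The cost is no extra data, but it is a change to a confirmatory analysis after recruitment began (13 December 2024). It should therefore be a dated amendment, made before any outcome data are seen by arm. The contrast gives up almost all power for a transient mid-course difference (about 0.03 against 0.74); the supportive trajectories would still show one.

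As an editorial correction only, in the last clause of the first paragraph under Dosing schedule and administration, replace TAU with continuous, so that it refers to the continuous and partial reinforcement groups.

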### Exploratory analyses

In addition to the confirmatory analyses, exploratory analyses will be conducted to examine potential associations between the primary outcomes and various secondary and moderating variables, including demographic characteristics (eg, age, gender), psychometric measures (eg, depression, anxiety), biological markers (ie, blood, saliva) and ecological momentary assessments (ie, itch ratings, treatment satisfaction). These analyses are exploratory in nature and are intended to generate hypotheses for future research.

### Missing data handling

All primary analyses will follow the intention-to-treat (ITT) principle, including all patients who received at least one active dose of the study medication and completed the acquisition phase (ie, attended visits 0–2). Patients meeting this criterion will be included in the analysis with all available data up to the point of dropout. By contrast, individuals who only attended the baseline assessment (visit 0) will be excluded from longitudinal modelling due to the absence of any post-baseline intervention exposure (ie, no medication or conditioned stimulus was administered). Missing data will be addressed using Full Information Maximum Likelihood (FIML) as the primary estimation approach. FIML leverages all available data points, including partially observed cases, by estimating model parameters based on the observed-data likelihood, without imputing missing values. This method is particularly suitable for complex mixed-effects models and preserves statistical power while minimising bias under the assumption of data missing at random (MAR).

Given the structured nature of data collection, where all assessments are completed on-site prior to medication administration, only a low proportion of missing data is expected. Reasons for missed visits (eg, illness, psychological burden) will be documented systematically through physician–patient contact and follow-up communication. In addition, a wide range of psychometric, demographic and clinical variables (eg, depression, anxiety, acute stress, treatment satisfaction) is collected, which increases the possibility that missingness is conditionally random (ie, MAR) and can be accounted for by observed data.

To empirically evaluate the MAR assumption, we will conduct logistic regression analyses to identify variables that significantly predict the occurrence of missing data. If no such variables are found, the originally specified analysis model will be estimated using FIML, without the inclusion of auxiliary covariates, thereby ensuring consistency with the pre-specified hypothesis structure.

However, if significant predictors of missingness are identified, multiple imputation (MI) will be employed as a complementary strategy. In this case, auxiliary variables will be included in the imputation model only, while the analysis model will remain unchanged. This allows for the modelling of potential MAR mechanisms without introducing auxiliary covariates into the hypothesis-driven analysis, thereby preserving the interpretability of the predefined main and interaction effects.

To ensure sufficient information for reliable imputation, only participants with at least 7 out of 10 observed time points (ie, ≤30% missingness) will be included in the MI procedure. Participants with fewer than 7 observed time points will not be imputed but will remain in the FIML-based analyses in line with the ITT principle. In these cases, parameters will be estimated solely based on the likelihood of the available observations, without extrapolation.

A comparison between estimates obtained via FIML and MI will serve as a sensitivity analysis, evaluating the robustness of results under different plausible missing data assumptions, while maintaining a clear separation between hypothesis testing and missing data handling.

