### Analysis plan

All statistical analyses will be conducted using R^64^ (V.4.1.1.; R Core Team, Vienna, Austria) within RStudio^65^ (RStudio Team, Boston, MA).

Confirmatory hypotheses will be tested using linear mixed models, assuming approximate normality of random effects and residuals. If model diagnostics indicate substantial violations of distributional assumptions, generalised linear mixed models with appropriate link functions and distribution will be applied based on the observed characteristics of the data.

Each model will include Group as a between-subject factor and Time (10 levels, one per visit) as a within-subject factor. The Group factor represents the treatment conditions (TAU, partial reinforcement and continuous reinforcement). The number of Group levels varies by hypothesis and will be specified within each hypothesis section. Random intercepts for participants will be included to account for individual differences. Random slopes will be added if they significantly improve model fit, as evaluated by likelihood ratio tests and information criteria (ie, Akaike Information Criterion, Bayesian Information Criterion).

Main effects and Group × Time interactions will be examined depending on the respective hypotheses. Pairwise comparisons of estimated marginal means will be conducted where appropriate, with Holm-adjusted p values used to control for multiple comparisons, particularly given the unbalanced group sizes. A significance level of α=0.05 will be applied for all confirmatory tests.

#### Hypothesis 1

We hypothesise that both experimental treatments (pooled across partial and continuous reinforcement) will be non-inferior to the TAU group regarding average reductions in itch, PASI and DLQI scores from pre-measurement to post-measurement. Non-inferiority testing will be embedded within the linear mixed model framework. One-sided 95% CIs will be computed based on model estimates. Non-inferiority will be concluded if the upper bound of the CI lies below the predefined MCID of 25%.^66^

#### Hypothesis 2

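### The variables cited in support of missing at random never enter the primary analysis, and the imputation that would use them depends on a weak significance screen

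*Protocol article*

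**What the plan says.** Four statements in the protocol article bear on this point.

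- **Primary method.** Under Missing data handling: "Missing data will be addressed using Full Information Maximum Likelihood (FIML) as the primary estimation approach". The stated justification is MAR.
- **Why MAR is thought plausible.** The same section says that "a wide range of psychometric, demographic and clinical variables (eg, depression, anxiety, acute stress, treatment satisfaction) is collected", and continues: "which increases the possibility that missingness is conditionally random (ie, MAR) and can be accounted for by observed data".
- **What the model contains.** Under Analysis plan: "Each model will include Group as a between-subject factor and Time (10 levels, one per visit) as a within-subject factor". Participant random intercepts are added, and random slopes if they improve the fit. No other covariate is named.
- **When the cited variables are used.** To examine MAR, "we will conduct logistic regression analyses to identify variables that significantly predict the occurrence of missing data". If none is found, "the originally specified analysis model will be estimated using FIML, without the inclusion of auxiliary covariates". Conversely, "if significant predictors of missingness are identified, multiple imputation (MI) will be employed as a complementary strategy". In that case the auxiliary variables enter the imputation model only, and the comparison of FIML with MI is a sensitivity analysis.

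Hypothesis 1 is decided by the one-sided confidence bound from the mixed model.

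**The concern.** Collecting a variable does not make data missing at random for an analysis that leaves the variable out. MAR is always relative to what the likelihood or the imputation model conditions on. The section offers its MAR argument for the data as a whole, but the argument applies only to the MI analysis, which may never be run.

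The trigger is also badly chosen. A non-significant screen on a small number of dropouts is weak evidence that the auxiliaries are irrelevant, yet it cancels the one analysis that would use them. Nor can the screen do what it is introduced for. A regression of missingness on observed variables says nothing about dependence on unobserved values, so a negative result does not show MAR.

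The direction matters because the trial tests non-inferiority. The protocol expects slower PASI improvement in the experimental groups and names psychological burden as a possible reason for missed visits. If distressed or dissatisfied patients leave the reduced-dose arms more often and would have done worse, a model without those variables makes these arms look somewhat better than they are.

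**Working it through.** The plan gives no figure for the screen or for bias, so there is none to reproduce. The check has three steps.

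**1. What each branch conditions on**

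| Screen result | Primary FIML conditions on | Is MI run? | Where the auxiliaries enter |
|---|---|---|---|
| Nothing significant | group, visit, observed outcome values | no | nowhere |
| Something significant | group, visit, observed outcome values | yes, as sensitivity | imputation model only |

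The primary column is the same in both rows.

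**2. How often the screen finds a real predictor**

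Inputs from the Sample size section: N = 168 and 10% dropout, so 168 × 0.10 = 16.8, about 17 dropouts. Assumed: one standardised predictor, a univariable logistic regression and a two-sided 5% test.

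Large-sample approximation: SE(log OR) ≈ 1/√(N·p·(1−p)) = 1/√(168 × 0.1 × 0.9) = 1/√15.12 = 0.257.

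- OR 1.5 per SD: ln 1.5 / 0.257 = 0.405/0.257 = 1.58. Detection ≈ Φ(1.58 − 1.96) = Φ(−0.38) ≈ 35%.
- OR 2.0 per SD: 0.693/0.257 = 2.70. Detection ≈ Φ(2.70 − 1.96) = Φ(0.74) ≈ 77%.

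Simulation at 10% dropout gives 30-36% for OR 1.5 and 72-78% for OR 2.0. One simulation (2,000 runs per setting) was repeated at other dropout rates:

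| Dropout | OR 1.5 | OR 2.0 |
|---|---|---|
| 5% | 20% | 45% |
| 10% | 30% | 73% |
| 15% | 44% | 86% |

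**3. How much bias is at stake**

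Assume a standardised auxiliary U that raises dropout (odds ratio OR per SD) and worsens the final score by g SD. To first order, the mean of U among completers is −p·ln(OR). If the same mechanism acts in both arms, with dropout p_R (reinforcement) and p_T (TAU), a completers-only contrast is biased by about −g·ln(OR)·(p_R − p_T).

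- g = 0.5, OR = 2, 20% against 5%: 0.5 × 0.693 × 0.15 = 0.052 SD in favour of reinforcement.
- Equal dropout in both arms: 0.

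FIML does better than completers alone because it uses each leaver's earlier visits. Results for ten-visit models, with last attended visit spread over visits 2-8:

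| Setting | Bias favouring reinforcement (SD) |
|---|---|
| Same mechanism in both arms, OR 2, 5% v 15-20%, random slopes | 0.002-0.024 |
| As above, random intercept only | 0.007-0.047 |
| U drives dropout in reinforcement only, OR 2, g 0.3-0.5, 5% v 15-20%, intercept only | 0.027-0.054 |
| Same mechanism, 10% in each arm | about 0 |

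If U drives dropout in the reinforcement arms only, equal 10% dropout still leaves 0.013-0.042 SD (OR 1.5-3). The extreme case, OR 3 with 5% v 20%, reaches 0.076 SD. Equality of dropout rates alone therefore does not remove the bias; the mechanism must be equal too.

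**The case against.** A likelihood analysis under MAR with MI as sensitivity is a common and respectable design. FIML still uses every earlier value of the modelled outcome, which carries much of what an auxiliary would add. The MAR sentence is hedged, and the text never claims that the auxiliaries are in the FIML model. All of this stands, and it is why the expected bias is small. It does not rescue the MAR argument for the primary analysis, nor the use of a p-value to decide whether the auxiliaries are used at all.

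Three stronger readings are tempting, and the document does not support them.

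- *A reader might infer that the non-inferiority test has a materially inflated error rate.* Larger bias, about 0.015-0.064 SD, appears when the data are reduced to two time points. The plan models ten visits, and the unequal dropout behind such figures is assumed: the protocol gives only 10% overall.
- *A reader might count chance triggers of the screen as harm.* With many candidate scales they would be frequent, but a chance trigger only adds a sensitivity analysis and leaves the primary result untouched. Missed predictors are what matter.
- *A reader might conclude that non-inferiority should require both the FIML and the MI bound to pass.* That would make a sensitivity analysis co-primary. It is a stricter design choice, not the repair of an error.

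The candidate list and threshold for the screen may properly sit in a statistical analysis plan that is not shown, and their absence is not part of this point.

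**Conclusion.** The point holds as a mismatch and a poor trigger. The variables offered in support of MAR stay outside the primary analysis in both branches. The only analysis that would use them is cancelled by a negative result from a screen that, at the protocol's own dropout rate, misses an odds ratio of 1.5 per SD about two times in three and an odds ratio of 2.0 about one time in four.

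The likely effect on the result is small: about 0.00-0.05 SD favouring the reduced-dose arms under 5% v 15-20% dropout and an odds ratio of 2, and about 0 if dropout and its mechanism are equal across arms. These sizes rest on assumed odds ratios, correlations and dropout patterns. No wrong non-inferiority conclusion is demonstrated. This is a cheap improvement to the plan, not a threat to its validity.

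**What to change.** 1. Delete the significance screen as the trigger for MI. Keep the logistic regressions as a description of who leaves.
2. Always run MI as a pre-specified sensitivity analysis of the non-inferiority comparison. Fix the auxiliary list in advance and choose it for expected correlation with the outcomes, for example earlier itch, PASI and DLQI, BDI-II, STADI-state, the stress VAS and the last available EMA treatment-satisfaction rating. Leave the analysis model unchanged and report the MI bound beside the FIML bound.
3. Reword the MAR rationale: the auxiliary variables support MAR for the MI analysis, while the FIML analysis assumes MAR given group, visit and the observed values of the modelled outcome.

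The cost is a change of wording and one imputation analysis in every case instead of some.

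The benefit is limited while MI is restricted to patients with at least 7 of 10 time points. A patient who attends every visit up to visit L has L + 1 points, so those last seen at visits 2-5 (3-6 points) are not imputed, and only those last seen at visits 6-8 (7-9 points) are. For the earliest leavers the auxiliaries would still go unused unless that rule is also revisited.
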